### Sample and laboratory procedures

In this study, bacterial swabs from the skin are obtained by a trained research assistant wearing non-sterile gloves. Sterile Copan MSwabs are used and samples will be collected for analysis of *S. aureus* colonization.

At the baseline assessment, swabs are taken from an affected part of the skin, preferably of the antecubital, popliteal, or neck fold. At all following visits, the swabs are taken from the same site. The skin surface is swabbed for 30 s.

Regarding the silver-coated textiles, there is a theoretical possibility for the adsorption of silver from the garment through the skin [19]. Therefore, silver excretion is assessed in urine in this group only. Morning urine of participants able to urinate in a urine cup will be collected and sent to a specialized laboratory. The urine of participants in the other groups will be collected as well in order to ensure that patients remain blinded.

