**Methods:**

This is a pragmatic randomized controlled double-blind multi-center trial comparing the effectiveness of antibacterial therapeutic clothing based on silver or chitosan as compared with non-antibacterial therapeutic clothing in patients with moderate to severe AD. A total of 165 participants, aged 0 to 80, diagnosed with moderate to severe AD are included. The study is performed in the Erasmus MC University Medical Center, University Medical Center Groningen, University Medical Center Utrecht, Amsterdam University Medical Centers, and St. Antonius Hospital Nieuwegein. Patients will be randomized 1:1:1 into one of the three intervention groups: group A will receive therapeutic clothing without antimicrobial agents, group B will receive microbial growth reducing therapeutic clothing based on chitosan, and group C will receive antimicrobial clothing based on silver. All therapeutic clothing is to be worn at night during the 12-month intervention period. Usual care is continued. The primary objective is to assess the effectiveness of antibacterial clothing (silver and chitosan group) as compared to non-antibacterial clothing assessed with the Eczema Area and Severity Index at 12 months compared to baseline. Secondary outcomes include between-group differences in physician- and patient-reported outcome measures, topical therapy use, *S. aureus* skin colonization, and safety. Data will be collected at baseline and after 1 month, 3 months, 6 months, and 12 months. A cost-effectiveness analysis will be performed.

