**Fig. 1 Fig1:**
[figure not shown]
Flowchart of the study design

All labels and brand names are removed from the therapeutic clothing (“unlabeled”). In addition, the clothing will be provided by mail by a third party to ensure blinding.

Blinded efficacy assessors are unaware of treatment allocation. Furthermore, the type of therapeutic clothing is not described in the digital patient file and the treating clinician has no access to the CRFs until study completion.

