### Safety

Safety will be assessed by registration of adverse events and urinary silver excretion in the silver group as described in the laboratory procedures.

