### Data collection, monitoring, and data analysis

ALEA will be used as a data management system [18]. Patient confidentiality will be ensured by using identification numbers. In a final stage, data from both management systems will be extracted to a SPSS dataset. Data management will be performed by the investigator and monitored by an independent monitor as predefined in the monitoring plan.

The data analysis will be conducted according to the intention-to-treat principle. The primary hypothesis is tested by means of linear mixed model analysis. The linear mixed model will use EASI as a dependent variable, and inclusion EASI, group, time, and time*group as independent variables; in addition, the EASI at baseline will be used as an additional covariate. As the time period between the visit varies (*t* = 1, 3, 6, and 12 months), time is defined as a continuous variable, in which we calculate the number of months from baseline. A two-sided alpha of 0.05 is used. Secondary outcome parameters will also be analyzed with linear mixed models. No interim analysis is planned, due to the low risks of participating in this study. Data will be available upon request.

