## Discussion

The ABC study is a pragmatic randomized controlled multi-center trial that compares the effectiveness of antibacterial therapeutic clothing with non-antibacterial therapeutic clothing in patients with moderate to severe AD. This study will provide high-quality evidence to inform clinical practice whether or not antibacterial therapeutic clothing is effective for AD. In addition, the cost-effectiveness of antibacterial clothing will be evaluated.

This study will also provide useful insights in the treatment of AD during a longer period. Data concerning the use of topical corticosteroids, adherence to the clothing, and use of other therapy will be available for analysis. In addition, the fact that both children and adults will participate from five centers across the Netherlands will provide us with data that can be used to compare age differences and treatment differences across a semi-national level. In addition, this trial will be the first trial to monitor the safety of textiles with silver in patients with the abnormal skin barrier.

In conclusion, the ABC trial will assess the (cost-)effectiveness and safety of antibacterial therapeutic clothing with chitosan and silver over a treatment period of 12 months in patients with moderate to severe atopic dermatitis.

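### Urinary silver is assayed in the silver arm only, so a raised level could not be attributed to the garment, although control urine is already collected

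*Protocol article*

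**What the plan says.** Under Sample and laboratory procedures, the article explains that silver might in theory pass from the fabric through the skin, and that for this reason "silver excretion is assessed in urine in this group only". Morning urine is taken from those who can use a cup and goes to a specialized laboratory. For groups A and B: "The urine of participants in the other groups will be collected as well in order to ensure that patients remain blinded". No other use of that urine is mentioned.

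The Safety section repeats the restriction: "Safety will be assessed by registration of adverse events and urinary silver excretion in the silver group".

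Two other places bear on how the result will be read. The Abstract (Methods) frames the secondary outcomes comparatively: "Secondary outcomes include between-group differences in physician- and patient-reported outcome measures, topical therapy use", in a list that goes on to *S. aureus* colonization and ends with safety. The Discussion says that "this trial will be the first trial to monitor the safety of textiles with silver in patients with the abnormal skin barrier".

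The visit schedule (Fig. 2) is not available in the text, so it is not known at which visits urine is taken or whether a pre-garment sample exists.

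**The concern.** Whether silver reaches the body from the garment is a causal question, and the trial has randomised arms that could answer it. Assaying one arm turns the measurement into an uncontrolled series.

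If silver-arm levels are raised, or rise over the 12 months, the trial cannot say how much comes from the clothing and how much from diet, environment or other products, or from a shift in the assay. This is the result for which an answer would matter most. The samples that would supply the answer are collected but, on the stated plan, yield no silver result. If they are not stored, the loss cannot be made good later.

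**Working it through.** The documents give no mean, SD, background level or safety threshold for urinary silver, so there is no plan figure to reproduce. The check is a decomposition of what each design identifies, followed by the assay count.

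**Inputs**
- Arms with silver assayed: 1 of 3 (Sample and laboratory procedures; Safety).
- Arms with urine collected: 3 of 3 (Sample and laboratory procedures).
- Group size 55, with 20% loss to follow-up assumed (Sample size; set for EASI, used here only as head counts).
- Group A garment: micro-modal and lycra. Group C garment: micro-modal and lycra with silver filaments, from the same manufacturer (Therapeutic clothing).
- Two assay time points: my assumption, because the schedule is not visible.

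**What each design identifies.** Let b0 and b1 be mean background excretion at the first and last collection, e0 and e1 the assay shift at those times, and g the garment contribution. Suppose for now that the first sample is taken before the garment is worn.

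1. Silver arm, first: b0 + e0.
2. Silver arm, last: b1 + e1 + g.
3. Change in the silver arm: g + (b1 - b0) + (e1 - e0). The three parts cannot be separated.
4. Change in group A, same batches: (b1 - b0) + (e1 - e0).
5. Difference, line 3 minus line 4: g.

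A baseline sample, if there is one, removes only the starting level. If there is none, the randomised difference at the last collection still gives g, since group A's last value is b1 + e1.

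**What the single arm can still show.** Background cannot be negative (b1 >= 0). With a valid assay (e1 negligible), line 2 gives g <= the silver-arm level. A low or undetectable level therefore bounds the garment contribution from above without any control arm. A raised level gives only a loose bound and no attribution.

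**Assay count for group A**
- Everyone gives urine at both times: 55 x 2 = 110.
- With 20% lost by the last collection: 55 x 0.80 = 44, and 55 + 44 = 99.
- Participants who cannot use a cup reduce both figures. The documents do not say how many they are.

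**Would the comparison be informative?** As an illustration, in SD units of the silver measurement, assume every retained participant gives a sample and use two-sided 0.05 and 80% power. The detectable difference is (1.960 + 0.842) x sqrt(2/n):
- n = 55 per arm: 2.802 x 0.1907 = 0.53 SD.
- n = 44 per arm: 2.802 x 0.2132 = 0.60 SD.

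Fewer samples would raise these values. Under the present plan the contrast has no estimate at all.

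**The case against.** The best defence is that the plan is open and consistent on this point. The Safety section defines the outcome in the same way as the laboratory section. The Abstract sentence is a summary that does not mention urinary silver, and adverse events are not limited to one arm, so a between-group safety comparison remains possible. The Discussion promises monitoring, which is less than a randomised estimate of uptake. All of this stands: the documents do not contradict themselves here. It does not answer the attribution problem, which arises from the stated design.

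Three stronger readings are tempting, and the documents do not support them.

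- A reader might infer that any urinary silver result would be uninterpretable. That goes too far, because a low level sets an upper bound, as shown above.
- A reader might infer that assaying one arm reveals allocation, particularly since "Data management will be performed by the investigator and monitored by an independent monitor". The article does not say where, or by whom, silver-arm samples are selected. The laboratory or an unblinded third party could do it. The article also states that "Blinded efficacy assessors are unaware of treatment allocation" and that "the treating clinician has no access to the CRFs until study completion". Sample coding and custody are details that a condensed article leaves to the full protocol.
- A reader might treat the 110 of 165 participants (67%) without a silver result as the size of the problem. That figure only restates two arms out of three and measures neither bias nor lost precision.

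**Conclusion.** The point holds in a limited form. Because silver is assayed only in group C, a raised or rising level cannot be attributed to the garment, and no between-group difference in silver excretion can be estimated. A low or undetectable level would remain useful as an upper bound, given a valid assay.

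The effect is confined to one secondary safety measure, and the primary EASI analysis is not affected. No size in silver units can be given, because the documents contain no silver data. The conclusion rests on the text, which states the one-arm assay in two sections, and does not depend on whether a baseline sample exists. Since the control samples are already being collected, this is a cheap improvement that should be made. It is not a flaw that threatens the trial.

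**What to change.** Keep and store the group A urine. Assay it at the first and last scheduled urine collection, under coded labels that do not show the arm, in the same batches as the silver-arm samples. Withhold results until unblinding, subject to any safety-alert arrangement in the full protocol, on which nothing is proposed here. In the Safety section, define the urinary-silver outcome as the silver-minus-control difference with a 95% confidence interval, alongside the silver-arm levels themselves. Group A is the natural comparator because its garment shares manufacturer and base fabric with the silver garment.

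The cost is sample storage and at most about 110 extra assays, assuming two time points. No additional visit or patient procedure is needed. The storage decision is the urgent part, because discarded samples cannot be recovered.

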### Primary outcome

The primary endpoint in this study is the difference in disease severity measured by the EASI [15] between the clothing without antimicrobial agents (control group) and microbial growth reducing/antimicrobial clothing based on chitosan or silver (intervention groups) at 12 months compared with baseline.

#### Secondary outcomes

Secondary outcomes include physician- and patient-reported effectiveness, degree of impetiginization, patient-reported quality of life, *S. aureus* colonization, use of topical corticosteroids and antibiotics, cost-effectiveness, and safety. Figure 2 provides an overview of the measurements per visit.

**Fig. 2 Fig2:**
[figure not shown]
SPIRIT diagram of study procedures. *Optional

### Physician-reported outcomes

The effectiveness of the therapeutic clothing will be assessed by using the EASI and Investigator Global Assessment (IGA) [20] and IGA for impetiginization in atopic dermatitis. Eczema severity will be assessed by a blinded rater. EASI is a validated scale recommended by the Harmonising Outcome Measures for Eczema (HOME) initiative [21] as an outcome for eczema severity. The final EASI captures erythema, excoriation, edema, lichenification, and body surface area. The IGA impetiginization is an outcome measure for impetiginization in atopic dermatitis that still needs validation.

### Patient-reported outcomes

The Patient Orientated Eczema Measure (POEM) [22], pruritus visual analogue scale (VAS) [23], pain VAS, sleep disturbance VAS, and AD control measured by the recap of atopic eczema (RECAP) [24] questionnaire will be used as patient-reported outcome measures.

Health-related quality of life (HRQoL) for patients suffering from a skin disease will be measured by using the Dermatology Life Quality Index questionnaire (DLQI) [25] in adults, Children’s DLQI in children, and Infants’ DLQI in infants. The TNO-AZL quality of life questionnaires (Preschool Children’s Quality of Life, Children’s Quality of Life, and Adult Quality of Life) [26] and EuroQol questionnaires (EQ-5D-Y and EQ-5D-5L [27]) will be used to measure the overall quality of life.

In addition, the Dermatitis Family Impact (DFI) [28] and Family Dermatology Life Quality (FDLQI) [29] questionnaires will be used to assess the impact of AD on the patients’ family and/or partner and a specific questionnaire consisting of Likert and VAS scales will be used to assess patient satisfaction with the therapeutic clothing as treatment for AD.

### Adherence to therapeutic clothing

A weekly questionnaire will be used to evaluate the adherence to the therapeutic clothing.

### Topical corticosteroid use

The amount of topical corticosteroids (TCS) use will be derived from a weekly questionnaire. Participants are asked to fill out the number of days, frequency per day, and name of TCS that are used. The difference in the amount and TCS potency between groups will be compared as a marker for the effectiveness of the therapeutic clothing.

### *S. aureus* colonization

Skin colonization with *S. aureus* will be assessed as described earlier.

### Safety

Safety will be assessed by registration of adverse events and urinary silver excretion in the silver group as described in the laboratory procedures.

### Cost-effectiveness

The economic evaluation of the clothing without antimicrobial agents (control group) and microbial growth reducing/antimicrobial clothing based on chitosan or silver (intervention groups) will be calculated as the incremental cost-effectiveness ratio (ICER). The primary effect outcome measures will be the effectiveness of the therapeutic clothing assessed by using the EASI for the cost-effectiveness analysis (CEA) and quality-adjusted life years (QALY) for the cost-utility analysis (CUA). QALYs will be measured for a 1-year period, based on the Dutch tariff for the EQ-5D.

### Data collection, monitoring, and data analysis

ALEA will be used as a data management system [18]. Patient confidentiality will be ensured by using identification numbers. In a final stage, data from both management systems will be extracted to a SPSS dataset. Data management will be performed by the investigator and monitored by an independent monitor as predefined in the monitoring plan.

The data analysis will be conducted according to the intention-to-treat principle. The primary hypothesis is tested by means of linear mixed model analysis. The linear mixed model will use EASI as a dependent variable, and inclusion EASI, group, time, and time*group as independent variables; in addition, the EASI at baseline will be used as an additional covariate. As the time period between the visit varies (*t* = 1, 3, 6, and 12 months), time is defined as a continuous variable, in which we calculate the number of months from baseline. A two-sided alpha of 0.05 is used. Secondary outcome parameters will also be analyzed with linear mixed models. No interim analysis is planned, due to the low risks of participating in this study. Data will be available upon request.

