### Participants

The study population consists of patients of all ages with moderate to severe AD according to the criteria of Williams [14]. Participants are eligible with an Eczema Area and Severity Index (EASI) score ≥ 6 at baseline [15]. Patients are not eligible if treated with therapeutic clothing, oral antibiotics, systemic immunosuppressive agents, or UV therapy until 1 month before inclusion or if treated with topical antibiotics within 1 week before inclusion. Other exclusion criteria are anamnestically assessed kidney function impairment, pregnancy or pregnancy wish, hypersensitivity to silver, or evidence of past non-compliance to treatments or appointments.

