### Randomization and blinding

Randomization is carried out by the Erasmus MC University Medical Center. Included patients are stratified before randomization. Patients are stratified according to the severity in the strata “moderate dermatitis” (EASI 6.0–22.9) or “severe dermatitis” (EASI 23.0–72.0) [15] and according to age (0–5, 6–17, and >18 years). ALEA Clinical software will be used for randomization (random block size randomization, blocks of 3 and 6) [18]. An overview of the randomization procedure is provided in Fig. 1.

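### Randomisation is stratified by age band, but the primary mixed model has no age term, a small and cheaply recovered loss of efficiency; the age bands as printed also skip age 18

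*Protocol article*

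**What the plan says.** Protocol article, Randomization and blinding: "Patients are stratified according to the severity in the strata “moderate dermatitis” (EASI 6.0–22.9) or “severe dermatitis” (EASI 23.0–72.0"), and "according to age (0–5, 6–17, and >18 years"). That makes 2 × 3 = 6 strata, with allocation in random blocks of 3 and 6.

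Protocol article, Data collection, monitoring, and data analysis: "The linear mixed model will use EASI as a dependent variable, and inclusion EASI, group, time" and the time-by-group interaction as independent variables; "in addition, the EASI at baseline will be used as an additional covariate". Age does not appear in this list, and no other section adds it. For the secondary outcomes the same section says only that linear mixed models will be used and lists no covariates.

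On eligible ages, the abstract says "A total of 165 participants, aged 0 to 80, diagnosed with moderate to severe AD are included", and the Participants section says "The study population consists of patients of all ages with moderate to severe AD".

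**The concern.** Stratified allocation makes the arms more alike on the stratification factors than simple randomisation would. If such a factor is prognostic, the treatment estimate varies less from trial to trial than a model without that factor assumes. The model then reports a standard error that is too large, intervals that are too wide and p-values that are too high, and part of the precision obtained by stratifying is lost. Severity is not affected, because continuous baseline EASI is in the model. Age is.

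This is not a matter of detail left to an unseen analysis plan, because the article itself names the model's terms. Age could plausibly matter: patients range from infants to 80 years, the sponsor chose age as a stratification factor, and the Discussion expects to compare age groups.

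A second, smaller matter is that a band ending at 17 followed by one starting above 18 leaves age 18 unassigned, although 18-year-olds are eligible.

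**Working it through.** **Inputs from the article (Sample size; Data analysis):** SD 13, difference 6.6, correlation 0.6, two-sided alpha 0.05, power 0.80, 20% loss to follow-up, 55 per group. Evaluable per group: 55 × 0.8 = 44.

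**Input assumed:** R², the share of baseline-adjusted EASI variance explained by age band. The article gives no figure. The range used is 0.05 to 0.15, with 0 as the limiting case.

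**Step 1. The plan's own figure.** A two-sample t-test with d = 6.6/13 = 0.51 needs 62 per group. The variance factor for the mean of four post-baseline visits is (1 + 3 × 0.6)/4 = 0.70. This gives 61.9 × 0.70 = 43.3, rounded up to 44, and 44/0.8 = 55. The stated 55 is reproduced, and this calculation does not involve age.

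**Step 2. Reported standard error at 12 months without age.** Single-visit ANCOVA approximation: SE = 13 × √(1 − 0.6²) × √(2/44) = 10.4 × 0.2132 = 2.217. Nominal power is Φ(6.6/2.217 − 1.96) = Φ(1.017) = 84.5%. This is an approximation to the planned longitudinal model, not a figure from the article.

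**Step 3. True standard error under stratification.** With age balanced across arms, true SE = 2.217 × √(1 − R²). The formulas are:
- excess of the reported SE: 1/√(1 − R²) − 1
- true type I error without age: 2 × [1 − Φ(1.96/√(1 − R²))]
- power without age: Φ((6.6 − 1.96 × 2.217)/true SE)
- power with age: Φ(6.6/true SE − 1.96)

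| R² | True SE | Reported SE too large by | True type I error | Power without age | Power with age | Gain (points) |
|---|---|---|---|---|---|---|
| 0 | 2.217 | 0% | 0.050 | 84.5% | 84.5% | 0 |
| 0.05 | 2.161 | 2.6% | 0.044 | 85.2% | 86.3% | 1.1 |
| 0.15 | 2.044 | 8.5% | 0.034 | 86.5% | 89.8% | 3.3 |

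The comparison must be made within a row. Setting 86.3% or 89.8% against 84.5% would ignore that stratification has already lowered the true variance of the unadjusted estimate.

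**Step 4. Sensitivity to the variance factor.** With the factor 0.70 that reproduces 55, SE = 13 × √(0.70 × 2/44) = 2.319. Power goes from 81.8% to 83.2% at R² = 0.05 and from 83.2% to 87.0% at R² = 0.15. The gain is about 1 to 4 points, the same order. The excess in SE and the type I error are as in the table, because they depend only on R².

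**Step 5. Which contrast is tested.** An age main effect is constant within a patient. Under a random-intercept structure, the standard error of the time-by-group coefficient comes from within-patient variation and is essentially unchanged by adding age. The figures above therefore apply to a model-based group difference at 12 months.

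**Step 6. Age bands.** 0–5 and 6–17 cover ages 0 to 17, and >18 covers 19 upward. Age 18 is in none of them.

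**The case against.** The strongest reply is that nothing here threatens validity. Randomisation protects the group contrast, and leaving out a balanced factor neither biases it nor inflates alpha. The planned size meets its 80% target without age. That stands: a reader might infer that the primary result would be invalid or biased, and the article does not support that.

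The evidence that age is prognostic is thin, and this also stands. The Background's statement that about 70% of childhood disease clears before adolescence concerns a course over years. The same section describes most patients as mild. This trial follows moderate to severe patients for 12 months with baseline EASI already adjusted for, so an R² near zero is equally compatible with the text. If age instead alters the course over time, a main effect alone would not capture that.

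The bound >18 is most naturally a slip for 18 and older. A reader might infer that 18-year-olds could not be randomised or that the randomisation system is misconfigured. The article does not show how the system was set up, so only a check of the wording is justified.

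Finally, the article lists no covariates for the secondary models, so no omission is shown there.

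What survives is that the model's terms are spelled out, a stratification factor is not among them, and adding it costs almost nothing.

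**Conclusion.** The point holds as a modest efficiency matter. The primary model leaves out a factor used to stratify randomisation. If age band explains 5 to 15% of the baseline-adjusted variance, the standard error of the 12-month contrast is overstated by about 2.6 to 8.5%, the nominal 5% test runs at about 4.4 to 3.4%, and about 1 to 3 points of power are forgone. These figures rest on the assumed R², close balance on age in the evaluable patients, 44 evaluable per group and the single-visit ANCOVA approximation. They shrink to near zero if age is not prognostic or if only the slope interaction is tested. The stated sample size is unaffected.

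The gap at age 18 is a probable wording error. It has no stated effect on the analysis, since age is not in the model as written, but it would matter once the age stratum is added.

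**What to change.** Before unblinding, add the age stratum used at randomisation (three levels) as a fixed effect in the primary linear mixed model. Do the same in the secondary models for consistency.

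Reconcile the printed age bands with what was programmed in the randomisation system, and restate them so that every eligible age falls in exactly one band. Check the system before changing anything in it.

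The cost is two degrees of freedom and a wording correction. No extra patients or data are needed, because age is already recorded for randomisation.

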## Methods

### Design and setting

The ABC study (AntiBacterial Clothing study) is a pragmatic, multi-center, double-blind, randomized controlled trial. The study aims to investigate the effectiveness of antibacterial therapeutic clothing based on silver or chitosan as compared with non-antibacterial therapeutic clothing in patients with moderate to severe AD. The study will be performed at the department of dermatology of the Erasmus MC in close collaboration with the departments of dermatology of the University Medical Center Groningen, University Medical Center Utrecht, Amsterdam University Medical Centers, and St. Antonius Hospital Nieuwegein. Both enrollment and the follow-up visits will take place at these five locations.

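### The primary model omits the age stratum used in randomisation and the centre; adding both would be a cheap gain in precision and corrects no bias

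*Protocol article*

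**What the plan says.** All points are from the Methods of the protocol article.

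- **Design and setting:** five hospitals take part, and "Both enrollment and the follow-up visits will take place at these five locations".
- **Randomization and blinding:** "Patients are stratified according to the severity in the strata" moderate or severe, "and according to age (0–5, 6–17, and >18 years"). Allocation uses "random block size randomization, blocks of 3 and 6". Centre is not named as a stratum.
- **Physician-reported outcomes:** "Eczema severity will be assessed by a blinded rater". The article does not say whether each site has its own rater or raters are shared.
- **Data collection, monitoring, and data analysis:** the primary linear mixed model has EASI as the dependent variable and "inclusion EASI, group, time, and time*group as independent variables"; in addition, "the EASI at baseline will be used as an additional covariate". "A two-sided alpha of 0.05 is used". Secondary outcomes are also to be analysed with linear mixed models. No random effect or covariance structure is given.

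The severity stratum is a cut of baseline EASI, so baseline EASI in the model represents it. Nothing listed represents the age stratum or the centre.

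**The concern.** Two separate issues arise from the same list of model terms.

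**Age stratum.** Stratified blocks make the arms nearly balanced on age class, so the true sampling error of the treatment contrast no longer contains the age component. A model without age leaves that component in its residual variance. The reported standard error is then larger than the true one, the confidence interval is a little too wide and the test a little conservative. The precision gained by stratifying is not used.

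**Centre.** Allocation is not balanced within centre. If centres differ in 12-month EASI after baseline adjustment, whatever chance imbalance arises between arms carries part of that difference into the estimate as extra random error. A centre term would remove it.

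What is at stake is precision on the primary comparison. The Discussion section expects the data to support comparisons by age and across the participating centres, so the authors themselves regard both factors as of interest.

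**Working it through.** **The plan's own figure.** The Sample size section gives SD 13, difference 6.6, alpha 0.05, power 0.80, correlation 0.6, five measurements and 20% loss. For the mean of *m* follow-up scores the variance factor is (1 + (m − 1) × 0.6)/m. With m = 4 this is 2.8/4 = 0.70, and

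n = 2 × (1.960 + 0.842)² × 13² × 0.70 / 6.6² = 42.6, so 43 per group.

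The small-sample t correction adds about one, giving 44, and 44/0.8 = 55. The stated 55 per group is reproduced, and this point does not challenge it.

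**Set-up for the checks.** Expected completers: 165 × 0.8 = 132, or 44 per arm. The contrast is pooled active (88) against control (44) at month 12, adjusted for baseline. Residual variance is 13² × (1 − 0.6²) = 108.2, so SD 10.4, and the standard error is 10.4 × √(1/44 + 1/88) = 1.92. Simulations used six strata, blocks of 3 and 6, and 4,000 runs per setting. This single-visit comparison stands in for the repeated-measures model.

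**Age stratum.** The share of residual variance explained by age is assumed; the documents give none. With perfect balance the reported standard error is too large by a factor 1/√(1 − share): 1/√0.95 = 1.026 and 1/√0.90 = 1.054. Simulation, where incomplete blocks leave slight imbalance:

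| Age share (assumed) | Model without age: reported SE | True SE | Overstatement |
|---|---|---|---|
| 5% | 1.92 | 1.88 | 1.92/1.88 = 1.02 |
| 10% | 1.92 | 1.84 | 1.92/1.84 = 1.04 |

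Formula and simulation together give about 2 to 5%. At 10%, type I error without age is 0.041. With age added, the reported SE is 1.82 against a true 1.84, and type I error is 0.052. If age has no effect, adding it costs essentially nothing (1.918 against 1.917).

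**Centre.** The intraclass correlation (ICC) of baseline-adjusted EASI and the centre sizes are assumed. With five equal centres, the SD of the centre contribution to the estimate is about √(ICC × 108.2 × 0.8 × (1/44 + 1/88)), where 0.8 = 1 − 1/5. This gives 0.24 EASI points at ICC 0.02, 0.38 at 0.05, 0.54 at 0.10 and 0.77 at 0.20, against a target of 6.6. Empirical standard errors without and with fixed centre terms:

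| ICC (assumed) | Equal centres | Unequal (50/20/15/10/5%) |
|---|---|---|
| 0 | 1.902 → 1.925 (+1.2%) | 1.942 → 1.974 (+1.6%) |
| 0.05 | 1.919 → 1.911 (−0.4%) | 1.968 → 1.947 (−1.1%) |
| 0.10 | 1.902 → 1.856 (−2.4%) | 1.882 → 1.859 (−1.2%) |
| 0.20 | 1.867 → 1.735 (−7.1%) | 1.817 → 1.701 (−6.4%) |

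The mean model-based standard errors at ICC 0.10 fall from 1.905 to 1.855 (−2.6%) and from 1.892 to 1.855 (−2.0%). At ICC 0 they rise from 1.923 to 1.954 and from 1.925 to 1.956 (+1.6% each).

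Across all centre settings, type I error is 0.044 to 0.057 with or without the centre term, and mean bias is within simulation error of zero. Power at 6.6 points without a centre term is 0.918 to 0.946.

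**What baseline EASI already does.** A constant scoring shift at a centre appears at baseline and at follow-up. With a baseline slope of 0.6, a share 1 − 0.6 = 0.4 of it remains. Differences in care that arise after baseline are not removed in this way.

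**The case against.** The strongest reply is that the article does not give the whole model. A linear mixed model needs a random effect or a covariance structure, and none is stated, so a random centre intercept could sit in a fuller document. That stands for the random part. It does not reach the age stratum, which would be a fixed covariate and is absent from the listed independent variables and covariate.

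A second reply is that the centre gain rests on an unknown ICC and may be nil or slightly negative. That also stands, and it is why centre is the weaker half of this point.

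Three stronger readings are tempting, and the documents do not support them.

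- A reader might infer that omitting centre biases the result. Randomisation is valid without centre: the estimate is unbiased on average, type I error stays near 5%, and ordinary chance imbalance is already reflected in the standard error.
- A reader might infer that scoring and steroid use are decided site by site and that nothing in the analysis deals with this. The Intervention section refers usual care to a treatment guideline, the article does not say raters are local, and baseline EASI removes part of a persistent scoring difference.
- A reader might infer that the trial gives up the equivalent of some 16 of its 165 patients. That corresponds to a variance saving of about 10% (165 × 0.10 = 16.5) at an assumed ICC of 0.15, the top of one assumed range. The documents give no ICC.

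**Conclusion.** The point holds as a minor matter of precision. The age stratum is the firmer part: it restricts the randomisation, is missing from the listed terms, and can be added at essentially no cost. The standard error is overstated by about 2 to 5% if age explains 5 to 10% of residual variance, and not at all if age is not prognostic. For centre, adjustment gains about 1% or less in standard error at ICC 0.05 or below and about 2 to 3% at 0.10, and fixed terms lose about 1.5% at ICC 0. These sizes rest on assumed age and centre effects, assumed centre sizes, 132 completers and a month-12 comparison. The primary test remains valid as written, and the sample size is unaffected.

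**What to change.** Leave the randomisation unchanged. Crossing centre with the six existing strata would give 30 cells for 165 patients, so a model term is the practical route. In the analysis section, add to the linear mixed models for EASI and the other continuous outcomes:

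- the age stratum (0–5, 6–17, adult), as recorded at randomisation, as a fixed covariate (2 degrees of freedom);
- centre, preferably as a random intercept, which largely avoids the loss when centres do not differ; otherwise as a fixed effect (4 degrees of freedom).

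State the random-effects part in the same place, and do so before unblinding so that the adjustment cannot look data-driven. The change is one line and uses values already recorded. The downside is a few degrees of freedom and, if centres do not differ, a very small loss of precision.
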